#### Control group: usual perioperative care

Participants allocated to the control group will receive usual care consisting of nutritional counselling and advice on smoking cessation and reduction of alcohol intake where relevant. No exercise advice will be provided, and patients will be instructed to maintain their normal daily activities.

To measure their objective level of physical activity during the preoperative period, study participants will be sent an activity monitor to wear in the week before their second assessment. Participants will be asked to maintain their usual activities during this period. All feedback and incentivising features on the monitor be deactivated.

### Treatment fidelity

To ensure the intervention is delivered according to protocol, we will create manuals of procedures and provide training to all staff involved in providing the study treatment and assessment of participants. To ensure standardisation, we will hold weekly meetings across the study sites. An independent researcher will audit a randomly chosen subset of patients to ensure adherence to the intervention program and the study protocol. This method was successful in our pilot study (92.7%) [33].

### Outcome measures

The following primary, secondary and other outcome measures will be collected across five time points: during the preoperative period (baseline assessment), within a week prior to the scheduled surgery (post-intervention), and postoperatively on the day of discharge from hospital, 1 month and 3 months after surgery (Table 2).

**Table 2 Tab2:**
[figure not shown]
Details of the schedule of enrolment, interventions and assessments according to Standard Protocol Items: Recommendations for Intervention Trials (SPIRIT) Diagram

#### Primary outcome measure

The primary outcome will be the proportion of participants developing ***in-hospital complications*** within the primary admission of the index surgery. The definition of each postoperative complication will be described per the Standardised Endpoints Core Outcome Measures in Perioperative and Anaesthetic Care (StEP-COMPAQ) group [34]. The primary outcome will be independently extracted from the hospital electronic medical records by two trial personnel at each study site blinded to group allocation. Disagreements will be resolved by discussion.

#### Secondary outcome measures

The secondary outcomes will be:(i)*Intensive care unit and hospital length of stay:* The duration of stay in the intensive care unit and hospital (in days); with the day of the index surgery considered as day 0. This information will be extracted from the hospital’s electronic medical records.(ii)*Quality of life*: measured by the Short Form 36 version 2 (SF-36v2®, Australian English) [35] at baseline (4-8 weeks preoperative), within the week before surgery, discharge day, and 3 months postoperative. The QualityMetric Health Outcomes™ Scoring Software will be used to obtain the final scores of the eight quality of life domains (physical functioning, role physical, bodily pain, general health, vitality, social functioning, role emotional, and mental health) and the two physical and mental summary scores.(iii)*Postoperative morbidity*: Further investigations on postoperative morbidity will be conducted as a secondary outcome measure:*Morbidity on postoperative day five and postoperative day 30*: Morbidity on postoperative day 5 (or the day of discharge if the participant is discharged earlier) will be assessed by the Postoperative Morbidity Survey (POMS) [36] and morbidity on postoperative day 30 will be captured using the postoperative complication definition recommended by the StEP-COMPAQ group [34]. The severity of each complication will be graded using Clavien-Dindo classification [37, 38]. The overall postoperative morbidity will also be expressed using the Comprehensive Complication Index (CCI) [39] which weights patients with multiple complications higher than patients with only a single complication yet of the same highest Clavien-Dindo severity grade.*Days at home within first 30 days after surgery (DAH-30)*: DAH-30 is a composite measure that accounts for the length of stay in the hospital following index surgery (Day 0), readmission to either the index or any other hospital, hospital discharge to a rehabilitation centre/hospital or nursing facility, and early deaths after surgery within a single metric. DAH-30 (number, value between 0 and 30) will be calculated using mortality and hospitalisation data from the date of the index surgery (day 0). For example, if a patient dies on postoperative day three, they will be assigned 0 for DAH-30. If a patient is discharged from the hospital on day six after surgery but is subsequently readmitted for 4 days before their second hospital discharge, the patient will be assigned 20 (=30-6-4) DAH-30. If a patient has complications and spends 16 days in the hospital, then is transferred to a nursing facility for rehabilitation, and spends 24 days there before finally being discharged to their own home, the patient would be assigned 0 (30-16-24 = − 10, set to 0) for DAH-30. If a patient dies within 30 days of surgery, irrespective of whether the patient has spent some time at home, DAH-30 will be scored as zero (0) [40, 41].(iv)*Health resource use (costs) and productivity losses*: Information on patient out-of-pocket and health system resource use (in Australian dollars, AUD), including the cost of the exercise intervention, will be collected (via follow-up questionnaires) from randomisation up to 3 months postoperative [11]. Information about the impact of the intervention and surgery on return to work and leisure activities will be used to inform productivity losses.

#### Other outcome measures

The following outcome measures will be collected:(i)*Functional capacity*: This will be measured by the CPET at baseline and within 1 week before the scheduled surgery [42]. Improved fitness will be defined as a positive change (≥10% on peak VO_2_, to account for inter-test variability) between CPET tests. Due to coronavirus disease (COVID-19) outbreaks in Australia, some clinics may not be able to see participants face-to-face, and access to CPET will be restricted and will not be uniformly available to all participants.(ii)Duke Activity Status Index (DASI): functional capacity will be measured at baseline and within a week before surgery. The DASI is a 12-item scale in the form of a self-reported questionnaire. The final score ranges from 0 to 58, where a higher score indicates higher functional capacity [43].(iii)*Self-reported physical activity*: Self-reported physical activity will be measured at baseline, within a week before surgery, and postoperatively on discharge day and after 3 months using the following tools: The Active Australia Survey [44], strength questions from the New South Wales Health population survey (https://www.health.nsw.gov.au/surveys/adult/Pages/default.aspx) and sitting questions from the International Physical Activity Questionnaire short form (IPAQ-SF) [45].(iv)*Objective physical activity*: Objective physical activity will be measured during the preoperative period using an activity monitor (Yamax EX510 Activity Tracker). For the intervention group, the activity monitor will be used during the whole intervention period and will provide real-time visual feedback. For the control group, objective physical activity will be collected using an activity monitor without any visual feedback during the 7 days before their second assessment (within 1 week before the scheduled surgery).(v)*Pain intensity*: Pain will be measured on a numerical pain rating scale (NPRS; 0 to 10 - where higher scores indicate worst symptoms) [46] at baseline, within a week before surgery, and postoperatively on discharge day and after 3 months.(vi)*Satisfaction*: Patient satisfaction of the intervention will be measured at the follow-up visit within 1 week before surgery using a self-reported questionnaire [33].(vii)*Fatigue*: Fatigue will be measured using the Fatigue Severity Scale at baseline, within 1 week before surgery and postoperatively on discharge day and after 3 months [47].(viii)*Five Times Sit-to-Stand Test*: Lower limb strength and function will be measured using the five times sit-to-stand test [48]. Patients will sit with arms folded across their chest and back against a chair. Then, patients will be instructed to stand up and sit down five times as quickly as possible, and the time taken to complete the test will be recorded. Due to COVID-19 outbreaks in Australia, participants will have the option to perform this assessment via video call.(ix)*Six-Minute Walk Test (6-MWT)*: Aerobic capacity and endurance will be measured using the 6-MWT. The test will be performed using the American Thoracic Society (ATS) guidelines indoors, along a flat, straight, enclosed corridor at each participating site [49]. The course will be 30 m in length and marked every three meters. The starting line and turning points will be marked and indicated to patients. Patients will be instructed to rest before beginning the test near the starting position, a forehead sensor and pulse oximeter will be attached to the patient for SpO2 and heart rate measurements, a timer will be set to 6 min, and a standardised guide will be used to provide instructions to patients. Patients will be informed that the objective of the test is to walk as far as possible for 6 minutes but are permitted to slow down, stop or rest when required. The distance walked will be recorded. Due to COVID-19 outbreaks in Australia, some clinics may not be able to see participants face-to-face. Thus, the 6-MWT assessment will be restricted and will not be uniformly available to all participants.(x)*Adherence to the study exercise program*: Defined as the percentage of exercise sessions attended/performed by those patients randomised to the preoperative intervention group. This will be collected using the clinician activity record. In addition, participants will receive the participant exercise diary to document their supervised sessions, home exercises, and physical activity advice. Participants will be contacted every week by the trials’ research officer to report their adherence to the preoperative program. Successful adherence to the preoperative program will be defined as ≥70% attendance of the supervised sessions.(xi)*Adverse events*: Defined as any undesirable event, such as injury, fall, severe breathlessness, new or progressive pain, and progressive fatigue will be collected preoperatively during or up to 60 min following the trial intervention or outcome assessment. Serious adverse events will be defined as life-threatening or result in disability, incapacity, hospitalisation, or death during or up to 60 min following the trial intervention or outcome assessment. In serious adverse events, the trial chief investigator and trial research officer will be notified immediately, and the incident reported to the relevant hospital ethics committee.(xii)*Treatment and Health Services*: Use of treatment and health services will be collected (via follow-up questionnaire) up to 3 months after surgery for the cost-effectiveness analysis. This would include information about treatments (physiotherapy, etc.), diagnostic imaging, visiting GP/specialist clinics, emergency department visits, and hospital readmissions.

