### Trial design

The proposed study is a multi-centre, assessor-blinded, pragmatic, comparative, RCT, with two parallel groups randomised in a 1:1 allocation. Participants will be randomised to (i) a progressive, preoperative exercise and education program delivered over 4 to 8 weeks prior to surgery or (ii) usual perioperative care alone (Fig. 1).

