**What procedures?**	**INDIVIDUALISED PREOPERATIVE EXERCISE AND EDUCATION PROGRAM (Intervention)** The intervention will be delivered using three main components: **1) Supervised, individualised, progressive exercise program**: The exercise program will consist of a 50 min individualised (one-to-one) training session with a physiotherapist or exercise physiologist, three times a week, for 4 to 8 weeks (range from 12 to 24 sessions). Each session will include warm-up, aerobic/anaerobic, resistance, respiratory exercises, and cooldown activities: ***a. Warm-up*** (~ 5 min): Low-intensity exercises (e.g., walking, cycling) ***b. Exercises*** (~ 40 min): *i. Aerobic and anaerobic exercises (~ 15-25 min)*: Cycle ergometer, treadmill, or rowing machine (high-intensity interval training based on their rated perceived exertion – M-Borg scale). This will be adjusted to the response of the patient as they progress through the exercise sessions. Considerable flexibility with the prescription of the high-intensity interval training will be adopted to allow for individual participant responses. Phase 1 (approximately 2 weeks): Exercise intensity focused on rated perceived exertion of 3 to 5 on the M-Borg Scale continuous 20 min session or 2 × 10 min sessions (Low intensity). This phase is ideal to prepare the patient for Phase 2. Sedentary patient may need to stay in this phase for approximately 2 weeks, while more active patients can move to Phase 2 sooner. Phase 2 (approximately 2-4 weeks): The intensity and duration of the exercise will be increased gradually. Exercises will be focused on a rated perceived exertion of 3 to 5 on the M-Borg Scale for 30-40 min (Moderate intensity). Once the patients can tolerate the Phase 2 sessions at the abovementioned M-Borg scores, they could progress to interval training at a higher intensity (Phase 3). Phase 3 (approximately 2-4 weeks): Introduce anaerobic high-intensity interval training at 5 to 8 on the M-Borg Scale (4 high intensity intervals on the M-Borg Scale of 5-8 lasting 4 min each with interval reduction of intensity on the M-Borg Scale of 3-5 for 4 min). *ii. Respiratory exercises* (~ 5-10 min): Deep breathing exercises alone or in a cycle with relaxed breathing, huff, and cough (Active Cycle of Breathing Technique). *iii. Resistance exercises (~ 10-20 min):* Squat, push-up, shoulder press, hamstrings curl, dumbbell deadlift, biceps curl, and overhead triceps extension (performed at 40-60% of the one-repetition maximum). ***c. Cooldown*** (~ 5 min): Stretching and flexibility exercises (Triceps, lower back, hip flexors, quadriceps, hamstrings, calf muscles, light jogging, walking, or stretching exercises), performed twice for 20-30 s. **2) Home exercises (4 times/week):** Home-based functional exercises will be prescribed by the treating physiotherapist or exercise physiologist to increase aerobic capacity and respiratory muscle function, including exercises with resistance provided by bodyweight, including push-ups, squats, step-ups. On the day’s participants are not attending the exercise training session, they will be instructed to perform the exercises for 30 min at home. **3) Daily physical activity advice**: In addition to home exercises, participants will be encouraged to walk continuously for at least 30 min daily, using an activity monitor (Yamax Power Walker EX-510). Participants will be asked to keep a daily diary of the number of steps per day and the number of home exercises performed during the preoperative period. The activity monitor will be provided by the study research team free of charge after the baseline assessment. The device will be collected from the patient at the following assessment (the week before surgery). Step count will be extracted from the activity monitor daily by the participant, and the research team will check all activity monitor data once the device has been returned. Access to this information will be limited to the patient and the research team. Once participation has been completed, the research team will delete all data from the activity monitor. The information stored on the devices will be erased. No one apart from the study investigators will have access to the data collected. No data collected from the activity monitor will be sent to any of the involved institutions. The results from the study will not be used to register the activity monitor. **USUAL CARE (CONTROL GROUP)** Participants allocated to the control group will receive usual care consisted of nutritional counselling and advice on smoking cessation and reduction of alcohol intake. However, no exercise advice will be provided, and patients will be instructed to maintain their normal daily activities.

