**Who provided?**	The intervention will be administered by local registered physiotherapists or exercise physiologists who will educate and provide high-intensity interval training, home exercises prescription and progression, and physical activity advice per the study protocol.
**How?**	The exercise program (supervised, individualised, progressive exercise program) will be individualised and delivered by registered physiotherapists or exercise physiologists. The home exercises will be prescribed by the registered physiotherapists or exercise physiologists and will be conducted at home, unsupervised. Likewise, the registered physiotherapists or exercise physiologists will give the daily physical activity advice to be completed by the participant, unsupervised.
**Where?**	The intervention will be conducted at private clinics, mainly in Sydney (New South Wales) and Melbourne (Victoria), Australia. However, as the trial is recruiting from major referral hospitals, it is expected that a small proportion of the patients will reside outside of New South Wales and Victoria. Therefore the intervention may also be conducted in private clinics in other Australian states.
**When and how much?**	The preoperative exercise and education program will be delivered 4-8 weeks before surgery and include: (i) Up to 24 sessions × 50 min: Supervised, high-intensity training. Individualised exercise prescription, progression, and follow-up with a local physiotherapist or exercise physiologist; (ii) Up to 32 sessions × 30 min: Unsupervised home exercise; (iii) Up to 56 walking sessions × 30 min: Advice to walk continuously (30 min daily).
**Tailoring**	The exercise program will be tailored to each participant based on a health assessment, considering patients’ current health status, physical activity level, presence of co-morbidities, and medical history.

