### Data and safety monitoring

An independent Data and Safety Monitoring Board (DSMB), led by an experienced physiotherapist, a gastrointestinal surgeon, and a statistician, will monitor adverse events and adherence to the protocol at regular intervals to ensure the safety of participants. The frequency of DSMB meetings and the stopping rules for the study will be defined a priori in a charter, in consultation with the DSMB members and study investigators.

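### Adverse and serious adverse events count only within 60 minutes of a session or assessment, so most of the preoperative period is outside adverse event recording and counts cannot be compared between arms

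*Protocol article*

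**What the plan says.** Other outcome measures, item (xi), lists the events of interest as "injury, fall, severe breathlessness, new or progressive pain, and progressive fatigue" and states that they "will be collected preoperatively during or up to 60 min following the trial intervention or outcome assessment". The next sentence defines serious adverse events and ends with the same limit: "hospitalisation, or death during or up to 60 min following the trial intervention or outcome assessment". Serious events go at once to the chief investigator and research officer, and are reported to the ethics committee.

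The Data and safety monitoring section gives the board its task: it "will monitor adverse events and adherence to the protocol at regular intervals to ensure the safety of participants". No other section widens the collection of adverse events.

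Trial design describes the experimental arm as "a progressive, preoperative exercise and education program delivered over 4 to 8 weeks prior to surgery". Table 1 gives up to 24 supervised sessions of 50 min, then "Up to 32 sessions × 30 min: Unsupervised home exercise", and up to 56 walks of 30 min. Controls receive no sessions. Both arms are assessed at baseline and again in the week before surgery. Randomisation and blinding places the baseline assessment before allocation.

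**The concern.** The window is fixed in the protocol text, so staff who follow it will log only what happens in or just after a session or assessment. Three consequences follow.

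- **Serious events.** A hospitalisation or death that arises the day after a session, away from any further session or assessment, does not meet the definition and does not trigger the notification and reporting steps. For an event that starts in a session and leads to admission some hours later, the sentence can be read either way: the limit may attach to the event or to its result.
- **Fit with the event list.** Progressive pain and progressive fatigue tend to build over longer than an hour, so a 60-minute window suits them poorly.
- **Unequal observation.** Controls have almost no window. A raw comparison of preoperative event counts would reflect time under observation as well as harm, and would tend to show more events in the intervention arm.

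The point matters most for a participant harmed before surgery who never reaches the index admission. That person has no primary outcome event either, because the primary outcome is confined to that admission.

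**Working it through.** The plan gives no figure for safety observation time, so there is none to reproduce. The check is the share of preoperative hours that falls inside a window.

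**Inputs.** From the article: 4 to 8 weeks of programme; 3 supervised sessions a week of 50 min; 4 home sessions a week of 30 min; walking of 30 min daily (Table 1); a 60-min tail after each; one preoperative assessment before randomisation and one after. Assumed, because the article does not say: each assessment lasts 1 to 3 h, so its window is 2 to 4 h.

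**Formula.** Coverage = sum over sessions of (duration + 60 min) ÷ total preoperative hours. Windows are assumed not to overlap, so intervention-arm coverage is an upper bound.

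| | 4 weeks | 8 weeks |
|---|---|---|
| Total hours | 28 × 24 = 672 | 56 × 24 = 1344 |
| Supervised | 12 × 110 min = 22 h | 24 × 110 min = 44 h |
| Home | 16 × 90 min = 24 h | 32 × 90 min = 48 h |
| Walking | 28 × 90 min = 42 h | 56 × 90 min = 84 h |
| All sessions | 88 h | 176 h |
| Supervised only, share | 22/672 = 3.3% | 44/1344 = 3.3% |
| All sessions, share | 88/672 = 13.1% | 176/1344 = 13.1% |
| All sessions + both assessments (4 to 8 h) | 92/672 to 96/672 = 13.7% to 14.3% | 180/1344 to 184/1344 = 13.4% to 13.7% |
| Control, one assessment after randomisation (2 to 4 h) | 2/672 to 4/672 = 0.3% to 0.6% | 2/1344 to 4/1344 = 0.15% to 0.3% |

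The Intervention group section encourages walking on weekdays, whereas Table 1 counts it daily. The table uses the larger number. With five walks a week the 8-week sum is 44 + 48 + 60 = 152 h, or 152/1344 = 11.3%.

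**Ratio of observation time after randomisation, intervention to control.**
- Supervised sessions only: from (22 + 4)/4 = 6.5 to (44 + 2)/2 = 23.
- All sessions: from (88 + 4)/4 = 23 to (176 + 2)/2 = 89.

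**How far time share speaks to harm.** If a share p of time is covered, the windows catch more than half of the events only when the hourly rate inside them exceeds (1 − p)/p times the rate outside. At p = 96/672 = 14.3% this is 6.0. At p = 48/1344 = 3.6% (supervised sessions plus two assessments of 1 h) it is 27. The article gives no event rates, so it cannot be said whether this holds.

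**The case against.** **Clock time is not risk.** The denominator includes sleep, and falls, injuries and breathlessness from exercise plausibly cluster around sessions. This stands. A reader might infer that most preoperative harm goes unrecorded, but without event rates the article supports only the statement about time.

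**Harm is collected elsewhere.** Items (v) and (vii) measure pain and fatigue at baseline and before surgery without restriction by arm. Resource use is asked about from randomisation, and item (xii) includes emergency visits and readmissions. A treating clinician who sees the participant three times a week can also notice pain or fatigue that has progressed since the last visit. This stands too: such harm may be recorded, though not necessarily as an adverse event. Service use is collected for costing, and nothing in the article sends these data to adverse event review.

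**Other safety comparisons remain valid.** A reader might infer that no between-group safety comparison can be made. That goes too far. In-hospital complications, day-5 and day-30 morbidity and days at home are collected alike in both arms, and complications are extracted blind. Analyses plans no between-arm test of adverse events. Only the preoperative counts under item (xi) are affected.

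**The monitoring board may see more.** Its charter is not shown, so one cannot say that it sees only these events.

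**An admission two hours after a session may still qualify.** If the limit attaches to the event and not to its result, it does. A reader might take the text to exclude such an admission outright, but the wording is ambiguous. A separate event the next day, outside any window, is excluded on both readings.

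**The trial intervention could mean the whole programme.** The intervention arm would then be covered throughout, a 60-minute tail would have little purpose, and the imbalance with controls would grow.

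**Conclusion.** The point holds in this form: the protocol fixes an adverse event window that leaves most of the preoperative period uncovered and is very unequal between arms. Coverage is at most about 13% in the intervention arm from sessions alone and about 14% with assessments, so about 86% or more is uncovered. In controls it is about 0.15% to 0.6% after randomisation. Observation time differs by a factor of about 6.5 to 89, depending on programme length, assessment length and whether unsupervised sessions count. These figures rest on non-overlapping windows and the assumed 1 to 3 h per assessment.

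Preoperative adverse event counts should not be compared between arms under this rule, and the serious adverse event definition needs rewording. The documents do not show that most harm is missed or that the trial's other safety information is invalid. The primary outcome, its analysis and the sample size are not affected. It is a cheap and worthwhile improvement to safety ascertainment.

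**What to change.** Amend item (xi) as follows.

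1. In both arms, record adverse and serious adverse events from randomisation to admission for index surgery.
2. Use what already exists: the weekly adherence contact in the intervention arm, the pre-surgery assessment in both arms, and medical records for admissions and deaths.
3. Take the 60-minute limit out of the serious adverse event definition. Keep it only as a flag for relatedness to a session or assessment.
4. Restrict any between-arm comparison to events ascertained identically, that is, at the pre-surgery assessment and from records. The weekly contact exists only in the intervention arm, so its events inform monitoring and not the comparison.

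**Cost.** A protocol amendment, a few questions at existing contacts, a record search, and more events to log and report. Recruitment began in June 2021, so for participants already treated ascertainment would be retrospective and not fully uniform. Some participants live outside New South Wales and Victoria, so admissions that do not appear in trial-site records would depend on participant report. Both limits should be stated when the safety results are reported.
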